### Plans to give access to the full protocol, participant-level data, and statistical code {31c}

Data will be available upon request. Requests for data reuse will be approved by the coordinating investigator. To gain data access, data requestors will need to sign a data access agreement.

## Oversight and monitoring

### Composition of the coordinating center and trial steering committee {5d}

This is an ongoing, monocentric study designed, executed, and coordinated at the Department of Medical Psychology | Neuropsychology and Gender Studies of the Faculty of Medicine and University Hospital Cologne of the University of Cologne in Cologne, Germany; therefore, there is no steering committee or stakeholder and public involvement group. The supervising principal investigator (author [name]) and head of the department (author [name]) provide day-to-day support for the trial and meet weekly with the research fellow coordinating and executing the study (author [name]). Trained research fellows as well as medicine and psychology student assistants from the department support data collection and data management.

### Composition of the data monitoring committee and its role and reporting structure {21a}

This study does not use a data monitoring committee. However, data entry and data checks are performed via the dual control principle by blinded members of the study team. Possible conflicts or uncertainties regarding data management or data monitoring are elaborated and discussed with the supervisory members of the study team (authors [name] and [name]).

### Adverse event reporting and harms {22}

So far, to the authors’ knowledge, no adverse events related to CT conduct have been reported in the literature. Therefore, adverse events related to CT conduct are not expected for this study. In the case that an adverse event occurs that is directly connected to CT participation, the events will be documented.

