#### Control group

To closely reflect clinical routine, participants of the CG continue their everyday life and care as usual after the baseline assessment. After a 5-week waiting period, participants complete the post-test in week 7 and the FU assessment at week 19. Following their FU assessment, participants receive 6 months of free-of-charge access to the CT program, including the CT schedule and the psychoeducational videos.

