### Criteria for discontinuing or modifying allocated interventions {11b}

At any time during the study, participants may discontinue participation at their personal request without giving any reason or written statement and without incurring any disadvantage. Specific risks or harms to the participant are not expected during study participation. However, participants might experience temporary fatigue due to the length and efforts of the neuropsychological assessments or CT or may feel distressed when confronted with possible deficits during the neuropsychological assessment or CT. Reported adverse events will be recorded and analyzed, and, if necessary, the protocol will be modified accordingly. A travel and residence insurance policy has been taken out for the duration of the study. In general, study allocation will not be modified retrospectively.

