### Provisions for posttrial care {30}

To date, the administration of CT and neuropsychological assessment has not revealed any adverse side effects, except for occasional signs of tiredness and mild exhaustion. Therefore, no harm is anticipated from CT implementation during the study, and no posttrial care provisions are needed.

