While the study has many strengths in place for the prevention or handling of potential challenges, certain limitations must still be acknowledged. First, since the study involves digital CT, participants must have access to a digital device with a reliable Internet connection and must be capable of using such a device to complete CT. This requirement may exclude some individuals with advanced PD, despite their eligibility based on disease stage. However, an advantage of the digital CT format is that it allows participation from individuals across Germany, including those who are immobile or unable to travel to the research facility. Second, the advanced PD stage may introduce additional challenges. These include disease-related complications, complex medical treatments, fluctuations of motor and non-motor symptoms—potentially affecting the ability to complete CT—and other complications that could impact the study’s progress or lead to a higher-than-expected dropout rate. Moreover, the complexity of care of people with advanced PD may lead to a higher rate of protocol deviations, which must be accounted for. Third, while this study aims to examine a participant pool that more accurately reflects clinical practice, it still excludes individuals with PD who are already suffering from dementia, thus precluding any conclusions on CT in people with PDD. Future research will need to build on this study’s findings to include and investigate individuals with PDD.

Fourth, since participants receive CT together with psychoeducational videos, any observed CT effects must be interpreted as resulting from the combined intervention, as the current study design does not permit separating the effects of CT from those of the psychoeducational component. Further studies using more elaborate statistical designs are needed to isolate specific contributions of each component.

In conclusion, the current study is, to the best of our knowledge, the first large-cohort study examining the effects of CT on people with PD in more advanced disease stages, thus offering class I evidence on the efficacy of digital CT in PD. CT could be an easy-to-administer, far-reaching, and safe intervention to strengthen cognitive functions in this patient group and prevent cognitive decline.

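### Two sections give different rules for which adverse events are recorded; under the narrower one, adverse events could not be compared between arms

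*Protocol article*

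**What the plan says.** Two places in the protocol article state what happens to adverse events.

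- **Criteria for discontinuing or modifying allocated interventions {11b}:** "Reported adverse events will be recorded and analyzed, and, if necessary, the protocol will be modified accordingly". No restriction by arm or cause is attached. The same paragraph expects some mild harms from the assessments as well as from the training: "participants might experience temporary fatigue due to the length and efforts of the neuropsychological assessments or CT".
- **Adverse event reporting and harms {22}:** "In the case that an adverse event occurs that is directly connected to CT participation, the events will be documented". This is the only recording commitment in the section devoted to harms. The section does not mention events in control participants or events with another cause.

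Three other places bear on the point.

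- **Control group:** "participants of the CG continue their everyday life and care as usual after the baseline assessment". Access to the training follows only after their follow-up assessment.
- **Discussion:** the closing paragraph says that "CT could be an easy-to-administer, far-reaching, and safe intervention to strengthen cognitive functions".
- **Secondary outcomes and statistical methods {20a}:** fatigue (FSMC) and depressive symptoms (BDI-II) are secondary outcomes, analysed along the same lines as the primary outcome.

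**The concern.** The two rules do not select the same events. Fatigue or distress after a long test session can occur in either arm. It is recordable under {11b} but falls outside the commitment in {22} unless someone connects it to the training. Staff following one section would build a different safety record from staff following the other.

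The narrower rule has two statistical drawbacks. It makes attribution a condition of being recorded, in a trial where participants know their arm. It also gives up the control arm for adverse events, although in advanced Parkinson's disease a concurrent control is the main way to separate intervention effects from the background of symptoms and fluctuations. A low count in the training arm under such a rule would say little about safety.

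**Working it through.** The plan states no adverse-event rate or safety sample size, so there is no figure to reproduce. The check is mainly a comparison of texts.

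**Step 1. Apply each rule to the same event.**

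| Event | Rule in {11b} | Commitment in {22} |
|---|---|---|
| Training-arm event linked to training | recorded | documented |
| Training-arm event not linked to training | recorded if reported | not covered |
| Control-arm event, e.g. fatigue after testing | recorded if reported | not covered |

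The rules agree on the first row only.

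**Step 2. Consequence if {22} governs.** Controls have no training before the end of follow-up, so none of the 70 planned control participants can meet the condition: 0 of 70 by construction. The training-arm count holds only events already judged related. The difference between the two would not estimate a treatment effect on harms.

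**Step 3. Consequence if {11b} governs.** Reported events in both arms are recorded and analysed, and the comparison is available.

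**Step 4. What a one-arm count could show.** With zero events among n participants, the one-sided 95% upper bound on the event rate is 1 − 0.05^(1/n). For n = 70 this is 4.2%, and for n = 64 it is 4.6%. Under {22} that bound would apply only to events attributed to training, not to all events.

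**Step 5. What two-arm capture would add.** The documents give no event rates, so those below are assumptions. With 70 per arm and a two-sided 5% level, power = Φ[(Δ − 1.96·SE0)/SE1]. Here Δ is the difference in rates, SE0 uses the pooled rate and SE1 the separate rates.

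For 10% versus 20%:
- SE0 = √(2 × 0.15 × 0.85/70) = 0.0604
- SE1 = √((0.10 × 0.90 + 0.20 × 0.80)/70) = 0.0598
- Power = Φ[(0.10 − 0.1183)/0.0598] = Φ(−0.306) = 38%

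| Assumed rates | Power |
|---|---|
| 10% vs 20% | 38% |
| 5% vs 15% | 50% |
| 10% vs 25% | 65% |
| 20% vs 40% | 74% |

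In the first case the 95% interval would be about 10 ± 1.96 × 5.98 = 10 ± 11.7 percentage points. Two-arm recording therefore gives an estimate with a wide interval, not a powered test.

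**The case against.** The strongest reply is that the sections can be read together: {11b} as the general rule and {22} as a specific promise about training-related events. The harms section does not say that other events go unrecorded. This stands, and it is why the loss of control-arm data is conditional. A reader might infer that only training-related events are recorded and that control-arm harms will not exist. The documents do not support this, because nothing says that {22} overrides {11b}.

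Four further replies also stand, wholly or in part.

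- **Who attributes.** A reader might infer that unblinded staff decide relatedness. Neither section says who decides this. An unblinded team member monitors training, while the post-test and follow-up examiners are blinded.
- **Other controlled data.** Fatigue and depressive symptoms are compared between arms as outcome scales, so it would be wrong to say that no harm can be compared. These are scores at visits, however, and do not replace a record of events.
- **The safety wording.** It is hedged, and safety is not named as an objective or outcome in the article. A reader might infer a planned safety conclusion that cannot be tested, but the article claims no such test.
- **Background statements.** {30} says that training and assessment so far "has not revealed any adverse side effects, except for occasional signs of tiredness and mild exhaustion", while {22} says that, to the authors' knowledge, "no adverse events related to CT conduct have been reported in the literature". One covers experience with training and testing together, the other published events tied to training. They sit awkwardly together but do not contradict each other.

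Forms, event fields and the wording of questions may properly be left to the full protocol. The finding rests on the two stated rules, not on the absence of such detail.

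**Conclusion.** The point holds as an inconsistency that should be resolved. The article states a broad capture rule in {11b} and a narrower commitment in {22}, and does not say which applies or to which arms.

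If {22} is followed, adverse events are filtered by attribution before recording, and the control arm contributes 0 of 70 by construction. No between-arm difference in adverse events could then be estimated. If {11b} is followed, that loss does not arise. The size of the problem therefore depends on which rule is in use, and the article does not show this.

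The MoCA analysis, the secondary outcome scales and the feasibility criteria are unaffected. The consequence is limited to the adverse-event record and to how much weight the cautious remark about safety in the Discussion can carry.

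**What to change.** Reword {22} to match {11b}:

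- Record every reported adverse event in both arms, in the same way and regardless of presumed cause.
- Assess relation to training afterwards, as a separate field.
- Report events descriptively by arm. If a difference with a 95% confidence interval is given, present it as an estimate and not as a powered test.

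If participants are asked about adverse events, protect examiner blinding. The question should come from the existing unblinded team member or sit on the take-home questionnaires, not be put by the blinded examiner, since training participants may mention their training when answering. Data entry is also blinded, so returned answers that could reveal the arm should go to the unblinded member.

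The cost is a change of wording, a small amount of extra recording and some unrelated events to list. Recruitment was expected to end in 2025 and follow-up runs to week 19, so the change may reach only the remaining visits. If the narrower rule was applied to participants already followed up, state this in the report and limit the safety wording in the Discussion accordingly.

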### Frequency and plans for auditing trial conduct {23}

Auditing is conducted on a weekly basis for internal reasons; a quarterly report is sent to the funder.

### Plans for communicating important protocol amendments to relevant parties (e.g., trial participants and ethical committees) {25}

Important modifications to the study protocol (e.g., changes to eligibility criteria, outcomes, or analyses) will be communicated to all relevant parties in a timely manner.

## Dissemination plans {31a}

Study results will be presented at national and international conferences and published in peer-reviewed scientific journals and will, therefore, be available to all relevant parties. Additionally, it is planned to publish the results of this study in a patient-oriented manner (e.g., in a nationwide self-help group journal).

## Discussion

This ongoing two-armed RCT examines the feasibility and effects of a 5-week digital CT in people with advanced PD, compared to those with PD receiving care as usual, while also exploring potential predictors of CT responsiveness. The body of literature assessing the effects of CT in PD is expanding, with preliminary evidence of positive effects [29, 32–34]; however, these findings are primarily based on heterogeneous studies with small sample sizes (*n* ≤ 76), including participants that are typically defined along cognitive inclusion criteria, therefore limiting the generalizability of these studies.

To address these challenges and to contribute significantly to this field, the current study incorporates several important aspects. First, to our knowledge, this study represents the first large-cohort investigation of both short- and long-term effects of a digital CT in people with advanced PD. Currently, no disease-modifying therapies or medications exist that may reduce the risk of cognitive decline or dementia for people with PD [45]. Moreover, managing PD in more advanced disease stages is complex, requiring careful consideration and a comprehensive approach that integrates both pharmacological and non-pharmacological treatments [45, 46]. Digital CT, with its potential to be widely accessible and its ability to be safely integrated into existing treatment regimens, holds promise as a long-term strategy to enhance cognitive function and potentially mitigate or delay cognitive decline [45, 109]. The large sample size of this study provides a robust foundation for statistically high-powered analyses, contributing valuable insights into the effects of CT for advanced PD. Additionally, the 3-month follow-up period will enable the exploration of sustained cognitive benefits and possible delayed effects, providing data on the potential for lasting cognitive improvement in this population.

Secondly, we evaluate the feasibility and acceptability of digital CT in advanced PD, thus examining whether digital CT interventions are suitable for more advanced PD stages in terms of technical handling as well as participants’ motivation and satisfaction with CT. Given that previous studies have shown high adherence to CT among people with PD [30], such interventions — particularly digital ones — have the potential to serve as a user-friendly complementary treatment option for individuals experiencing cognitive decline or those who wish to take preventive measures against it [37]. As there is currently no widespread availability of CT within the German healthcare system, digital CT, which can be performed at home, presents even greater opportunities for individuals with PD across various disease stages. If CT proves feasible and acceptable, this study offers evidence to support the integration of digital CT interventions into the daily lives of people with PD, especially for those in more advanced disease stages who may be limited in their mobility or those living in more rural areas, where it can be difficult to receive CT outside their homes. Integrating interventions like digital CT into their daily routines could enhance people with PD’s self-management skills by enabling them to actively participate in managing their condition [110, 111].

Third, this study seeks to identify possible predictors of CT responsiveness on an exploratory basis, with the goal of determining which individuals are most likely to benefit from CT. The existing literature on predictors of CT responsiveness is highly heterogeneous. Some studies suggest that cognitive baseline levels may predict CT responsiveness [38, 44, 49, 50], while other factors (e.g., age, education, motor symptom severity, and intelligence) have also been explored, with inconclusive results [38, 44, 51–53]. The present study may therefore provide deeper insights into the predictors of CT responsiveness, potentially facilitating the development of personalized CT interventions tailored to the specific needs of people with PD. Additionally, exploring these predictors may enhance our understanding of the mechanisms underlying CT effectiveness in PD, leading to more efficient resource allocation and targeted interventions across different stages of the disease.

Fourth, in contrast to previous studies on CT in PD, which primarily focused on participants' cognitive status [40, 65], this study adopts a more clinical perspective by recruiting participants based on disease severity. This methodological shift better reflects the realities of clinical practice, where people with PD are often categorized by their overall disease progression (e.g., severity of motor symptoms) rather than isolated cognitive metrics [112, 113]. Moreover, the use of a passive CG aligns with current clinical conditions, where the majority of individuals with PD do not receive CT unless they actively pursue it. By selecting a clinically relevant sample of individuals with PD at high risk for cognitive decline, this study may provide insights that could enhance comprehensive care strategies, particularly for individuals in more advanced stages of PD who are frequently underrepresented in existing research. Addressing this gap is essential for developing interventions that are applicable, easy to administer, and beneficial in real-world clinical settings.

Despite the abovementioned strengths of this study, certain challenges may arise during the execution of the study. One of the biggest challenges may be the recruitment of 140 individuals with advanced PD. To address potential difficulties in recruitment, a comprehensive recruitment plan using a phased approach was developed by the study team. The initial phase involves distributing flyers and handouts at the University Hospital Cologne, as well as reaching out to people with PD who have previously participated in studies at the primary study site and agreed to be contacted again for further studies. Additionally, the study is promoted on the website of the University Hospital Cologne and through repeated brief calls for participants at the “Parkinson’s Day for people with PD” event at the University Hospital Cologne. In the second phase, regional and nationwide self-help groups are contacted. If desired, members of the study team may give a short presentation (either digitally or in person) on the study and its background to these groups. In the third phase, the study team will reach out to supporting research institutes and PD clinics nationwide to assist with participant recruitment (e.g., by distributing flyers or promoting the study to potential participants). Taken together, this recruitment plan opens various communication channels that can facilitate recruitment and help achieve the goal of 140 participants.

A second challenge may be the risk of missing data due to the long battery of tests and the fact that this is administered by various members of the study team. To mitigate the potential for data loss caused by inadequate data collection or management (e.g., incorrect administration of tests during neuropsychological assessments or unusable data), all members of the study team receive comprehensive training in data collection and management, supported by standard operating procedures developed for and tailored to this study; all members will be supervised by the executing study team member (author [name]) as well as the supervisory study team members (authors [name] and [name]). In cases where complete study adherence is not possible, the study team tries to collect as much data as possible from the respective participant.

While the study has many strengths in place for the prevention or handling of potential challenges, certain limitations must still be acknowledged. First, since the study involves digital CT, participants must have access to a digital device with a reliable Internet connection and must be capable of using such a device to complete CT. This requirement may exclude some individuals with advanced PD, despite their eligibility based on disease stage. However, an advantage of the digital CT format is that it allows participation from individuals across Germany, including those who are immobile or unable to travel to the research facility. Second, the advanced PD stage may introduce additional challenges. These include disease-related complications, complex medical treatments, fluctuations of motor and non-motor symptoms—potentially affecting the ability to complete CT—and other complications that could impact the study’s progress or lead to a higher-than-expected dropout rate. Moreover, the complexity of care of people with advanced PD may lead to a higher rate of protocol deviations, which must be accounted for. Third, while this study aims to examine a participant pool that more accurately reflects clinical practice, it still excludes individuals with PD who are already suffering from dementia, thus precluding any conclusions on CT in people with PDD. Future research will need to build on this study’s findings to include and investigate individuals with PDD.

Fourth, since participants receive CT together with psychoeducational videos, any observed CT effects must be interpreted as resulting from the combined intervention, as the current study design does not permit separating the effects of CT from those of the psychoeducational component. Further studies using more elaborate statistical designs are needed to isolate specific contributions of each component.

In conclusion, the current study is, to the best of our knowledge, the first large-cohort study examining the effects of CT on people with PD in more advanced disease stages, thus offering class I evidence on the efficacy of digital CT in PD. CT could be an easy-to-administer, far-reaching, and safe intervention to strengthen cognitive functions in this patient group and prevent cognitive decline.

